## Oversight and monitoring

### Data monitoring

Given the low-risk profile of this trial and in line with EMA guidelines, an external data safety monitoring board is not required. However, due to the potential side effects of etidronate, safety will be periodically reviewed by an independent data safety monitoring board (DSMB). Interim safety analyses will be conducted at 6, 12, and 18 months, evaluating laboratory parameters and ophthalmological data (anti-VEGF injections). The interim analysis is performed by an independent statistician, blinded to the treatment allocation. The statistician will have unblinded access to all data and will report the results of the analysis to the independent DSMB. The DSMB, including at least a professor in biostatistics and a medical specialist, will discuss the results of the interim analysis and will issue binding safety recommendations to the ethics committee.

### Harms

Adverse events are defined as any undesirable experience occurring to a subject during the study, whether or not considered to be related to the investigational product (etidronate). All adverse events reported spontaneously by the subject or observed by the investigator or his staff will be recorded. An adverse event that meets the criteria for a serious adverse event (SAE) will be reported to the local ethics committee as an SAE. A SAE for this study is any untoward medical occurrence or effect that, whether or not considered or not be related to the investigational product that results in death, is life threatening, requires hospitalization or prolongation of existing hospitalization, results in persistent or significant disability or incapacity, is a congenital anomaly or birth defect or any other important medical event that, due to medical or surgical intervention, did not result in any of the outcomes listed above, but could have based upon appropriate judgement by the investigator. An elective hospital admission will not be considered a serious adverse event.

### Audit and monitoring

No independent audits are planned for this study. Oversight will be ensured through routine monitoring activities conducted by the TSF. These monitor visits aim to ensure protocol compliance, verify informed consent procedures, assess source data verification, and evaluate data quality and completeness. The TSF monitors will conduct their visits independently of the study investigators and sponsor. Any deviations or issues identified during monitoring will be documented and addressed in collaboration with the study team. Escalation to the sponsor or ethics committee will occur if required.

### Ethical considerations

The study will be conducted according to the principles of the Declaration of Helsinki (Fortaleza, Brazil, October 2013) and in accordance with the Dutch Medical Research Involving Human Subjects Act (WMO), the requirements of Good Clinical Practice (GCP), and this study protocol (Version 7.0, 2024). The study is approved by the Medical Ethical Review Committee, NedMec (registration number 21–552), as well as the CCMO. Any modifications to the protocol that may impact the conduct of the study, the potential benefit of the patient, or may affect patient safety, including changes of study objectives, study design, patient population, sample sizes, study procedures, or significant administrative aspects, will require a formal amendment to the protocol. Such an amendment will be agreed upon by the study team and approved by the Ethics Committee before implementation.

## Results

Participant recruitment commenced in April 2023, with anticipated results to be available in 2027. Findings will be shared through peer-reviewed publications and presentations at both national and international conferences.

## Discussion

The TEMP-PREVENT trial will provide insight into the effect of 24 months of treatment with etidronate in young adult patients with PXE.

Previously, the TEMP-trial has shown that a year of etidronate treatment in PXE patients gave a reduction in arterial calcification of 4% (interquartile range [IQR], − 11% to 7%) when compared to placebo. This trial did, however, exclusively enroll patients with measurable arterial calcification, comprising, therefore a relatively older and more profoundly affected study population. It remains uncertain to what extent arterial calcification can be halted in a young adult population. 

A young adult study population has the additional advantage that the retina is not yet, or at least to a lesser degree, affected by choroidal neovascularization and atrophy [45]. The TEMP trial showed a difference in neovascularizations between the etidronate (1) and placebo group (9); however, post hoc analysis showed this was likely not an effect of etidronate but could be explained by the unequal distribution of patients more at risk of CNV activity among the two groups [46]. Using newly developed techniques in measuring reflectivity of Bruch’s membrane in patients without extensive structural damage of the macula, the aim is to better study the effect of etidronate on ophthalmologic manifestations in PXE patients.

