A proof-of-concept study demonstrated that etidronate reduced soft tissue calcification in an *ABCC6* -/- mice model [17]. This finding was confirmed in a randomized, double-blind, placebo-controlled clinical trial in PXE patients [18]. After 1 year of treatment, arterial calcification had decreased by 4% (IQR, − 11% to 7%) in the etidronate group and increased 8% (IQR, − 1% to 20%) in the placebo group [18, 19]. Arterial calcification was, however, not a primary endpoint. Moreover, the trial included only PXE patients with extensive arterial calcification, resulting in a relatively older and more affected population. It is unclear if arterial calcification is equally inhibited in a young adult population with fewer PXE manifestations. Moreover, etidronate only inhibits the growth of calcification and does not reverse it, so prevention of further ectopic calcification early on may be even more beneficial than inhibiting it at a late stage. Another benefit of a young trial population is that calcification of Bruch’s membrane is better visible in eyes that show no gross structural damage to the macula, such as choroidal neovascularization or pigment epithelium or retinal atrophy, as often happens in later stages of PXE.

Therefore, in the TEMP-PREVENT trial, we aim to determine the effect of etidronate treatment in PXE patients with minimal or no existing arterial calcification on the development and progression of arterial calcification, and also on ocular calcification in Bruch’s membrane, dermatological calcifications, and cardiovascular outcomes.

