### Study population

Patients will be recruited from the UECP located in the University Medical Center Utrecht (UMCU) and by recruitment through (social) media, for example, using the UMCU website, the Dutch PXE Society, newsletters, yearly patient days, and conferences. In total, 76 patients will be recruited. To be eligible to participate in this study, a subject must meet the following inclusion criteria: (1) age between 18 and 55 years, (2) definitive or probable diagnosis of PXE according to the Plomp criteria [20], and (3) fertile women should take adequate contraceptive measures. Reasons for exclusion are the following: (1) patients unable or unwilling to sign for informed consent, (2) for women: pregnant, lactating, or fertile and wish to become pregnant within 3 years, (3) estimated glomerular filtration rate below 30 ml/min/1.73m^2^ according to the CKD-EPI equation [21], (4) known abnormality of the esophagus that would interfere with passage of the drug (e.g., esophagus stenosis), (5) chronic diarrhea (> 1/month), (6) known osteomalacia, (7) hypocalcemia (calcium < 2.20 mmol/L corrected for albumin), (8) vitamin D deficiency (< 35 nmol/L), (9) use of bisphosphonate in the last 5 years, (10) known sensitivity to etidronate, (11) any other medical or social condition that, at the discretion of the Principal Investigator, might put the subject at risk of harm during the study or might adversely affect the interpretation of the study data. The eligibility screening will be performed by the treating physician. Individuals withdrawn from the study (for any reason) will be replaced.

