Secondary endpoints are changes in dermatological, ophthalmological, vascular, laboratory, cognitive, and quality of life parameters. *Dermatological* outcomes are changes in elastin degradation and calcification in skin biopsies. A 3-mm punch biopsy will be taken from non-lesional skin, at least 2 cm from a pseudoxanthoma lesion, on the back of the neck just below the hairline, and under local anaesthesia. To ensure standardization and repeatability, a photograph of the biopsy site will be taken, and at the 24-month follow-up (M24), a second biopsy will be performed at least 2 cm from the original site to avoid scar tissue interference. The extent of elastin degradation will be scored on Verhoeff-Van Gieson stains, and the extent of calcification will be scored on Von Kossa stains [24]. All analyses will be performed by an experienced dermatopathologist. *Ophthalmological* outcomes are changes in best-corrected visual acuity and low luminance visual acuity, contrast sensitivity, changes in the infrared images, autofluorescence patterns, and the appearance of new choroidal neovascularisations on optical coherence tomography (OCT)-angiography, Bruch’s membrane reflectivity on high-definition spectral domain OCT, and the number of anti-VEGF injections. OCT is a non-invasive imaging technique requiring mydriatic eyedrops [25]. *Vascular* outcomes are changes in carotid intima-media thickness (cIMT) by ultrasound, which is a non-invasive measurement to establish the carotid atherosclerotic vascular disease and measures the thickness of the tunica intima and media of the carotid artery [26]. Moreover, changes in pulse wave velocity [27] and pulse wave analysis [28] are measured to reflect changes in arterial stiffness. Ankle-brachial index [29], the six-minute walking test [30], and the WELCH questionnaire [31, 32] are compared between baseline and 24 months of follow-up to reflect peripheral arterial disease. Moreover, changes in the pulsatility index of the intracranial carotid arteries and middle cerebral arteries by 7T-MRI are compared. The incidence of major adverse cardiovascular events (TIA, stroke, myocardial infarction, and/or cardiovascular death) is counted to see if etidronate lowers the risk of these events. *Laboratory* outcomes are changes in calcium, phosphate, ASAT, ALAT, eGFR, desmosin, and inorganic pyrophosphate [33]. *Cognitive outcomes* are changes in memory, attention, and executive function. Memory will be assessed with the Rey auditory verbal learning test with immediate recall, delayed recall, and recognition [34]. Attention will be tested with the Trail Making Test-A [35], Stroop Test reading and colour naming [36], and Digit Span Forwards WAIS-III [37]. Executive function will be tested with the Trail Making Test-B [35], Stroop Test colour-word Interference [36], Digit Span Backwards WAIS-III [37], Semantic fluency [38], and the Brixton Test [39]. Composite Z-scores will be calculated for the different cognitive domains using normative data from the Advanced Diagnostics Infrastructure (ANDI) [40]. The differences in change in cognitive functioning between baseline and follow-up will be compared between the intervention group and the control gro*up. Quality of life* outcomes are changes in EQ-5D [41], PROMIS 10 [42], PROMIS PF [43], and USER P [44].

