## Assignment of interventions

### Allocation

Randomisation will be performed 1:1 using computer-generated block randomization with variable block sizes by the Clinical Drug Research Unit of the UMCU. Participants and researchers are both blinded to treatment allocation. Participants are enrolled by the research physician. The research physician is not involved in the randomisation procedure.

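### The protocol attributes the earlier trial's CNV difference to unequal baseline risk, yet fixes no baseline CNV adjustment here; its reflectivity aim also has no matching set of eyes

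*Protocol article*

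**What the plan says.** **CNV history and endpoints.** The Discussion reports: "The TEMP trial showed a difference in neovascularizations between the etidronate (1) and placebo group (9"). It goes on to say that post hoc work made a drug effect unlikely and that the difference "could be explained by the unequal distribution of patients more at risk of CNV activity among the two groups". Outcome measures again lists "the appearance of new choroidal neovascularisations on optical coherence tomography (OCT)-angiography" and the number of anti-VEGF injections.

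**Allocation.** "Randomisation will be performed 1:1 using computer-generated block randomization with variable block sizes". No stratification factor is named.

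**Analysis.** Under Statistical analysis, change from baseline to 24 months is compared between arms for every primary and secondary endpoint, by intention to treat. Regression adjustment follows if relevant baseline differences appear, and adjusted and unadjusted results are both reported. No covariate is named, and what counts as relevant is not defined. Subgroups, if numbers allow, are by predominant phenotype (eye, skin or vascular).

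**The eye aim.** Background and rationale says that "calcification of Bruch’s membrane is better visible in eyes that show no gross structural damage to the macula", and the Discussion gives the aim as "measuring reflectivity of Bruch’s membrane in patients without extensive structural damage of the macula, the aim is to better study the effect of etidronate". Study population admits patients on "1) age between 18 and 55 years, (2) definitive or probable diagnosis of PXE according to the Plomp criteria" plus contraception for fertile women. None of the 3 inclusion or 11 exclusion criteria concerns the eye.

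**Available data.** Table 1 schedules infrared, autofluorescence and OCT-angiography images at M0 and M24, SD-OCT at M0, M12 and M24, and injection counts at every contact from M0.

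**The concern.** Baseline CNV risk is the one prognostic factor that the protocol itself holds responsible for a misleading result in the predecessor trial. One would expect it to be either balanced by design or adjusted for by a fixed rule. Here it is neither: adjustment depends on someone deciding, after seeing the baseline table, that a difference is relevant. If the arms differ moderately and the difference is not called relevant, the CNV and injection comparisons rest on an unadjusted contrast with the same weakness as before. Injection counts also feed the interim safety reviews described under Data monitoring.

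The second part concerns Bruch's membrane reflectivity. The stated aim refers to eyes without extensive macular damage, while the stated analysis includes everyone enrolled, up to age 55. The main result would then answer a somewhat different question from the one given as the reason for studying young patients.

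**Working it through.** The plan gives no figure for any eye endpoint, so the calculations below only illustrate size. The trial size (76, or 38 per arm) and the 33 per arm before dropout come from Sample size calculation. Prevalences and event rates are assumptions.

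**1. The plan's own figure.** The SD is not stated. From the earlier trial's interquartile ranges in Background and rationale, SD = 18/1.349 = 13.34 (etidronate) and 21/1.349 = 15.57 (placebo), pooled 14.50. Then n = 2 × (14.50 × 2.802/10)² ≈ 33 per arm, as stated. This concerns the CT endpoint only.

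**2. Chance imbalance in at-risk patients.** With K at-risk patients among 76 and 38 allocated to each arm, the number in one arm is hypergeometric (76, K, 38).

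| K (assumed) | Share of 76 | P(arms differ by 7 or more) |
|---|---|---|
| 15 | 20% | 8.2% |
| 23 | 30% | 13.3% |
| 31 | 41% | 16.1% |

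Odd values of K are used so that the threshold means the same in each row: the difference between arms has the same parity as K. At a threshold of 6 or more, K = 29, 30 and 31 give 15.6%, 24.0% and 16.1%. The 24% arises because only the even K can reach exactly 6, so it should not be read as a steep rise with prevalence.

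**3. Would an imbalance be noticed?** With K = 23, a split of 8 versus 15 (21% versus 39% of 38) has a two-sided exact p of 0.133. If relevance were judged by a significance test, this split would not trigger adjustment. The protocol does not say how relevance is judged.

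**4. Effect on the unadjusted comparison, with no drug effect.** Assume new CNV in 30% of at-risk and 3% of other patients. At 8 versus 15, expected cases are 8 × 0.30 + 30 × 0.03 = 3.3 and 15 × 0.30 + 23 × 0.03 = 5.2, a ratio of about 1.6 with an inert drug. False-positive rates of an unadjusted two-sided Fisher test at 0.05 are:

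| At-risk split | Simulation (40,000 runs) | Full enumeration |
|---|---|---|
| 11 v 11 | 0.9% | 1.0% |
| 8 v 15 | 3.5% | 3.4% |
| 7 v 16 | 5.5% | 5.3% |
| 5 v 18 | 12% | 11.9% |

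Fisher's test is conservative at these counts. A moderate imbalance therefore distorts the estimate but does not push the error rate above 5%; a severe imbalance does.

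**5. Precision of a restricted reflectivity analysis.** The standardised difference detectable with 80% power is 2.802 × √(2/m) for m patients per arm. It is 0.69 at m = 33. If 80%, 60% or 50% of patients had evaluable maculae (m = 26.4, 19.8, 16.5), it would be 0.77, 0.89 or 0.98. This is the cost of restriction and the reason to keep the all-eyes analysis beside it.

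**The case against.** Several points on the other side carry weight.

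- **Adjustment is provided for.** A reader might infer that CNV and injections are compared with no regard to baseline risk. That is not so: the adjustment clause covers a visible imbalance, both models are shown, and analysts are blinded, which limits steering of the choice. What stands is that the clause is conditional, names no covariate, and is triggered by observed imbalance rather than by known prognostic importance.
- **The text is hedged.** A reader might also infer that the protocol presumes undamaged maculae. It does not: it speaks of extensive damage and says that "the retina is not yet, or at least to a lesser degree, affected by choroidal neovascularization and atrophy". The age limit is its indirect means of selection, and better visibility is offered as a relative advantage. What stands is that aim and analysis set do not match, since the hedge itself allows for some affected eyes.
- **Damaged eyes may still carry signal.** Treating a share f of eyes as pure noise would give a sample-size penalty of 1/(1−f)², or 1.56 to 2.78 for f of 20% to 40%. Nothing in the documents says that such eyes carry no signal, so this is not claimed.
- **Details may sit elsewhere.** Eye-level analysis sets and covariate lists often belong in a full protocol or SAP, neither of which is shown. This limits the second part to a suggestion. It weighs less on the first, because the article does state an adjustment rule, and that rule is the conditional one.

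**Conclusion.** The point holds in a limited form. The protocol identifies unequal CNV risk as the likely explanation of an earlier signal, measures the same kind of outcome again without stratification, and leaves adjustment to a judgement made after baseline differences are seen. Adjusting in every case is the better rule and costs almost nothing.

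Under assumed prevalences of about 20% to 40%, a difference of 7 or more at-risk patients between arms has a probability of roughly 8% to 16%. Whether it would mislead depends on CNV rates that the documents do not give. The mismatch between the reflectivity aim and the population analysed is real but modest, and calls for an added analysis rather than a replacement. These are secondary endpoints; nothing here touches the primary CT comparison.

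**What to change.** Recruitment closed in December 2024, so eligibility and randomisation cannot change. The last visit is scheduled for December 2026, which leaves time to fix the analysis before unblinding.

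1. State that new CNV and anti-VEGF injections are compared between arms with baseline CNV status as a fixed covariate or stratum, whether or not an imbalance is seen. Grade that status, masked to allocation, from the M0 images already acquired. Name this as the main result and show the unadjusted one beside it. With few events expected, a single stratification factor is preferable to a longer covariate list.
2. Add a Bruch's membrane reflectivity analysis limited to eyes without extensive macular damage at M0. Write down the grading rule in advance, apply it masked to allocation, and define the set on baseline status only, so that no event after randomisation decides which eyes count. Report it beside the all-eyes analysis.

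The cost is a small grading effort, a few lines of analysis text, and fewer eyes in the restricted analysis. No new visit, procedure or patient is needed.

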## Trial status

The protocol version number and date are: Version 7.0, 24/06/2024. The recruitment of the first participant started on April 26, 2023. The last patient was recruited on December 4, 2024. The last patient visit of the study is scheduled for December 2026.

## Data Availability

Data can be made available upon request. The study team had access to the final trial dataset. There are no contractual agreements that limit access for our investigators.

## Abbreviations

CCMO: Dutch Central Committee on Research Involving Human Subjects
DSMB: Data safety monitoring board
GCP: Good clinical practice
PPi: Inorganic pyrophosphate
PXE: Pseudoxanthoma elasticum
SAE: Serious adverse event
UECP: UMC Utrecht Expertise Center for Pseudoxanthoma elasticum
UMCU: University Medical Center Utrecht
WMO: Dutch Medical Research Involving Human Subjects Act
